##### Mental health outcome

The EPDS and GAD-7 scores will be derived for each subject at enrollment and at every subsequent follow-up. We will calculate the mean and median scores for each group and conduct between-group analyses. Additionally, we will compare the changes between baseline and follow-up scores for each group (within-group analysis), followed by a between-group comparison of these changes.

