There is emerging evidence that the gut–brain axis (GBA) is a reasonable target for the management of PDA disorders. The GBA is a recently realized phenomenon in medicine, suggesting continuous bidirectional communication between the gut microbial community and the brain, a requirement for achieving and maintaining gastrointestinal homeostasis and cognitive function. Dysbiosis—an imbalance in bacterial composition—has been implicated in many disorders, including mental health (8). Thus, optimizing the health of the gut microbiome (i.e., treating dysbiosis) may be a logical approach to preventing and treating mood disorders.

Pregnancy itself has been associated with changes in the gut microbiome driven by immunological, hormonal, and metabolic changes—these changes are proinflammatory in nature, leading to an increase in cytokines and leukocytes and the recruitment of other immune cells (macrophages, natural killer cells, etc.) that aid in angiogenesis, transport of respiratory gases and nutrients between mother and fetus, and protection against pathogens (9). Interestingly, certain changes in the composition of the microbiome have been associated with various diseases during pregnancy, such as gestational diabetes, preeclampsia, fetal growth restriction, and obesity (9). Likewise, these changes are thought to be at least partially at play in perinatal mood disorders. A 2022 mini-review examined the correlation between perinatal depression and dysbiosis of the mother’s microbiome and reported dysbiosis as a likely precipitating factor in the development of psychiatric disorders during pregnancy (10). Emerging evidence suggests that nutritional interventions, with fish oils, probiotics, and prebiotics may play a favorable role in neuropsychiatric outcomes (11–16) and that some of these effects are mediated at least partially, by restoring eubiosis.

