##### Microbial response to diet and supplementation

First, we will assess the microbiome response to each intervention within each group by comparing changes in microbiome composition between baseline (preintervention) and follow-up visits (visits 2–6). The gut profile will be compared between all four arms at each follow-up. The within-group changes from baseline will be compared between groups.

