#### Statistical analysis

Should the trial succeed and we continue to recruit for a larger trial, the following statistical plan will be used to compare mental health outcomes between the groups: we will use mental health scores as the primary outcome and an intent-to-treat approach for these analyses.

Participants lost to follow-up will be assumed to have lost interest/commitment to the study and will be excluded from the analysis. Those who discontinue treatment will still be included.

Between-group differences for EPDS/GAD-7 scores will be analyzed using analysis of covariance (ANCOVA), with group membership as the independent variable, EPDS/GAD-7 as dependent, and pharmacotherapy, exercise status, and any form of psychotherapy as covariates.

The interaction effect between the O3FA and probiotics model will be analyzed and reported in each model. Alternative models will be used if the assumptions of ANCOVA are violated. If differences are found between groups, appropriate *post-hoc* analyses will be conducted to identify where the differences lie. Within-group differences at each time point will be analyzed using repeated measures ANOVA. Data from each follow-up will be compared to baseline scores. EPDS/GAD-7 scores will be the dependent variables, and follow-up times will be our independent variable.

Each stool sample will undergo shotgun metagenomics for taxonomic and functional output readings. A comprehensive analysis of all findings will be conducted by an experienced bioinformatics expert at Zymo Research. All researchers involved in the stool analysis will be blinded to the type of intervention. The relationship between each intervention and the relationship to EPDS and GAD-7 scores will be analyzed and reported by an experienced bioinformatician.

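### Within-arm change from baseline is labelled the response to intervention and tested by repeated measures ANOVA, although it mixes natural perinatal change with any treatment effect

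*Protocol article*

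**What the plan says.** Three sections of the protocol article plan comparisons with baseline inside each arm.

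- **Microbial response to diet and supplementation:** "we will assess the microbiome response to each intervention within each group by comparing changes in microbiome composition between baseline (preintervention) and follow-up visits". Here the before–after change within an arm is itself named the response to the intervention. The section then adds two between-arm steps: "The gut profile will be compared between all four arms at each follow-up", and a comparison of the within-arm changes across groups.
- **Mental health outcome:** "We will calculate the mean and median scores for each group and conduct between-group analyses". It then says "we will compare the changes between baseline and follow-up scores for each group (within-group analysis", and the sentence goes on: "followed by a between-group comparison of these changes".
- **Statistical analysis:** the between-group ANCOVA on EPDS/GAD-7 comes first. Later: "Within-group differences at each time point will be analyzed using repeated measures ANOVA", with each follow-up set against baseline.

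The Background states: "Pregnancy itself has been associated with changes in the gut microbiome driven by immunological, hormonal, and metabolic changes".

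None of these sections calls the within-arm results descriptive or says what may be concluded from them.

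**The concern.** Enrolment is at 12–35 weeks of gestation. Of the five follow-up visits, one is in the third trimester and four are at 1, 3, 6 and 9 months postpartum. A woman's change from baseline thus usually spans the end of pregnancy and delivery. By the article's own account pregnancy shifts the gut microbiome, so composition can be expected to move between these time points with or without supplements.

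For the mood scores the article makes no equivalent statement, but its design makes drift plausible. Women must be stable at entry, with current depression and anxiety ruled out by the MINI; the Background cites relapse rates of 40%; and co-treatments may change during follow-up.

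If within-arm change is called the response and is tested, an arm can show a significant response when the treatment does nothing. A significant change in one arm and not in another also invites being taken for a difference between arms. Under Outcomes measured, the article relates the microbial response to each intervention to mental health scores, in search of signals that would support a larger trial. It therefore matters which quantity carries that name.

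**Working it through.** The plan gives no alpha, standard deviation or effect size for these outcomes, so there is no figure of its own to reproduce. What follows is an illustration.

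**1. What each comparison estimates.** Write the expected change from baseline in arm k as δ + τₖ, where δ is natural perinatal change and τₖ is the treatment effect.

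- Within-arm test: tests δ + τₖ = 0. With τₖ = 0 it still rejects whenever δ is large enough.
- Between-arm comparison of changes: (δ + τⱼ) − (δ + τₖ) = τⱼ − τₖ. A drift common to the arms cancels. Randomisation makes δ equal in expectation. For an arm filled by preference, δ may differ.

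**2. Inputs.**

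- Arm size 25: the Discussion gives 75 women in the intervention arms and 25 in control. Equal intervention arms, 75 / 3 = 25, are an assumption.
- Two-sided 5% level: assumption.
- Natural shift d, in SDs of the change score, 0.2 to 0.5: assumption.
- Treatment effect: zero in every arm.

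**3. Within-arm rejection rate.** A one-sample t-test on change stands in for one follow-up-versus-baseline contrast. Its statistic follows a non-central t with n − 1 = 24 degrees of freedom and non-centrality d√n. The critical value is 2.064.

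| Shift d (SD of change) | d√25 | P(p<0.05), no treatment effect |
|---|---|---|
| 0.2 | 1.0 | 16% |
| 0.3 | 1.5 | 30% |
| 0.5 | 2.5 | 67% |

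**4. Between-arm rejection rate.** In 20,000 simulated pairs of arms with n = 25 each, a common shift of 0.5 SD and no treatment effect, the two-sample t-test on the changes rejected in 5.1%. The within-arm test in the same simulation rejected in 66.9%, which agrees with the table.

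**5. Larger trial.** The ANOVA is outlined for a larger trial whose size is not stated. At d = 0.3 and an assumed 50 per arm, the within-arm rate is 55%; at an assumed 100 per arm it is 84%. The rate rises with n because the test is detecting a real change, only not one caused by treatment.

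**The case against.** The strongest reply is that the remedy is largely in the plan already. The mental health sentence ends in a between-group comparison of the changes, the microbiome section compares both profiles and changes between arms, and the statistical section puts the between-group ANCOVA first. The Discussion frames its expectations as contrasts between arms and gives the control arm the role of showing the size and direction of change. All of this stands. A reader might infer that the trial will conclude efficacy from within-arm change alone; the documents do not support that, since no section says so.

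Three further limits also stand.

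- Only the Statistical analysis section names a within-group test. The mental health and microbiome sections speak of comparing and name no test.
- The Background's statement on natural change concerns the microbiome, not EPDS or GAD-7. For the scores, drift is plausible but not asserted.
- The primary outcome is process evaluation. The link between microbiome and mood is exploratory, and the ANOVA belongs to an outline for a later trial.

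What the reply does not remove is the label and the separate test. A valid between-arm comparison does not make a within-arm p-value valid evidence of response. Beside it, the plan would carry two competing definitions of response. The temptation is greatest for fish oil. Every intervention arm receives it and the control arm is filled by preference, so no randomised contrast isolates it, and within-arm change cannot fill that gap.

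**Conclusion.** The point holds in a limited form. Labelling uncontrolled within-arm change as the response to intervention, and testing it by repeated measures ANOVA with no limit on interpretation, attributes natural perinatal change to treatment if followed as written. The planned between-arm comparisons are sound on this point: among randomised women they remove a drift common to the arms and hold about 5%.

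Under the stated assumptions, within-arm tests give p<0.05 in 16% to 67% of arms with no treatment effect. That range rests on a natural shift of 0.2 to 0.5 SD and 25 women per arm. The shift has no source in the article, so the figures show the mechanism and do not forecast this trial. Because the aims affected are secondary and exploratory, this calls for a clarification of analysis and wording. It does not challenge the feasibility objective.

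**What to change.** - **Microbial response to diet and supplementation:** define response to intervention as the between-arm difference in change from baseline. Limit causal statements to women randomised among Gutopia, Gutboost and Gutless. Report the preference-assigned control as a non-randomised comparison, and label it so.
- **Mental health outcome and Statistical analysis:** report within-arm trajectories descriptively, as means with intervals at each visit, in place of the within-group significance tests.

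The cost is the loss of within-arm p-values, which cannot show a treatment effect in this setting. The between-arm comparison is already planned, the ANCOVA need not be replaced by another model, and the control arm need not be dropped. No data collection changes.

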#### Microbiome profiling

We will be partnering with Zymo Research, a California-based company. Zymo Research is a globally established biotechnology company and industry leader in the fields of epigenetics, microbiomics, and the emerging Next-Gen Sequencing space, with facilities in many countries and a global distribution network. The stool collection kits will be purchased from Cederlane^®^ an Ontario-based distributor of Zymo’s products. The fecal collection kits purchased feature DNA/RNA shield technology, which allows for accurate and safe collection and preservation of samples for downstream analysis. The kits will include a fecal collection tube, a feces catcher, a biohazard bag, gloves, and multilanguage instructions.

The stool will be collected from each patient at baseline and every follow-up visit. The self-collection will occur at participants’ homes, and they will be provided with all shipping materials and instructions to send their collected samples by mail to our institution. All samples will be stored onsite at CCNM according to guidelines provided by Zymo Research. A room in the Schad Naturopathic Clinic that is earmarked for research will be used to store samples; this room is accessible only by keycode, has temperature-monitoring devices, and is marked with applicable biohazard signage. Using their recommended kits, the samples can be stored at ambient temperature for a period of up to 5 years. In total, each patient will contribute six samples throughout the study period. Samples can be shipped as one batch at the end of the study period to Zymo Research in Irvine, California.

This study will not examine blood biomarkers for fatty acid intake.

The following outline analysis is aimed at a larger efficacy trial. Should this feasibility trial succeed, we will continue enrollment with the goal of assessing the efficacy of the interventions and specifically the impact of each on the gut microbiome and mental health outcomes. The following paragraphs provide a brief outline of these secondary aims.

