## Methods

### Trial design and setting

This is a single-centered, partially randomized placebo-controlled double-blind feasibility trial with three intervention arms (Gutopia, Gutboost, and Gutless) and one active control. In total, 100 pregnant women with a history of depression and/or anxiety/PDA attending Sunnybrook Hospital Clinics in the Greater Toronto Area will be recruited.

Participants in Gutopia will receive a daily dose of both investigational products and dietary counseling on increasing dietary fiber. Participants in Gutboost will receive a daily dose of both investigational supplements, while participants in the Gutless arm will receive fish oil and a placebo. Participants in Gutless and Gutboost will be blinded to the status of the placebo/probiotic they will be receiving. The study member interacting with the patients will also be blinded to the treatment group the participant is assigned to. Participants who fully consent to receiving both investigational products, including placebo, will be fully randomized to one of the intervention arms. Participants not willing or able to take a placebo or probiotics will be assigned (not randomized) to the appropriate group that accommodates their preferences/needs. Participants unable or unwilling to take any of our investigational products will be assigned to the active control arm. Women in the control arm will receive standard care offered to all obstetric patients seen at the hospital.

The study involves six study visits, all of which can be conducted virtually every 3 months from the time of enrollment (**Figure 1**). The last study visit will happen between 9 and 12 months postpartum. Two of the study visits will occur during pregnancy [enrollment (visit 1) and third trimester (visit 2)], with the remaining occurring at 1, 3, 6, and 9 months postpartum. At all study visits, information on diet, mental health, physical activity, and sleep quality will be collected. Additionally, all participants will provide a stool sample at each visit, using our stool collection kits, which will be shipped to or dropped off at our center.

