#### Exclusion criteria

Prepregnancy BMI > 30.Low income (unable to afford basic daily needs).Single parents without any kind of family support.Having a child with significant mental/physical disability.Previously diagnosed with other major mental health disorders.Taking prescription medications (other than SSRIs/SNRIs/TCA).Smoking and recreational drug use.Dietary restrictions or allergies to fish oils.Repeated antibiotic use.Women are unable to switch to study brand supplements.Multiparous women with young children (i.e., one or more children less than 4 years of age at the time of delivery).No/low English reading comprehension.

Our inclusion criteria allow for antidepressant/anxiety use. Medication use is an important prognostic factor that can significantly alter mental health outcomes. Hence, the number of patients treated with an antidepressant/anxiolytic needs to be equally distributed among all arms. To achieve this, we will use stratified randomization using two strata (treated vs. untreated) through a computer-generated process using permuted blocks of three and six. The process will be repeated separately for untreated participants.

Preexisting and diagnosed major mental health disorders will be determined at the time of screening using a modified version of the Mini International Neuropsychiatric Interview (MINI). The MINI, conducted by a trained research team member, will allow for confirmation of a history of anxiety/depression and an absence of current anxiety/depression and other major mental health disorders (bipolar, schizophrenia, psychosis, etc.).

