### The intervention

Participants in all intervention groups will receive a 200-ml bottle of Genestra brand Super EFA Forte Liquid Omega-3 Fatty Acid. Participants will be instructed to take 1 teaspoon a day with a meal.

Participants in the Gutopia and Gutboost intervention groups will receive HMF Maternity Probiotic Formula, a Genestra brand. Participants will be asked to take one tablet daily with food.

Details of both supplements are provided under Investigational products in the following section.

Only participants in Gutopia will receive a dietary intervention. Intervention is geared toward increasing gut-friendly foods via a flexible dietary plan aimed at increasing daily uptake of prebiotic and probiotic foods. A registered dietitian will use baseline food questionnaire data provided by each subject at enrollment to devise strategies and recommendations for increasing intake of pre/probiotic foods. The target goal is to include at least 35 g/day of fiber and at least one to two servings of fermented foods daily. The dietary intervention will also include recommendations minimizing highly processed foods high in sugar and fat. To improve adherence and accountability, weekly follow-ups by phone, virtual meeting, or email will be conducted by a trained study team member until patients have reached a level of confidence in attaining goals. During each follow-up, the study team will monitor the level of adherence to the study RD’s recommendations. These follow-ups will be designed to provide encouragement while helping patients address and prevent triggers that jeopardize their fiber intake.

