The placebo capsules will contain 48% maltodextrin, 48% microcrystalline cellulose, 2% magnesium stearate, and 2% silicon dioxide. The capsule shell will be composed of hydroxypropyl ethylcellulose and will be identical in capsule shape and packaging to the probiotics. Participants will be instructed to take one capsule a day with food, 2–3 hours before or after taking an antibiotic in the event that one is prescribed through ancillary usual care received separate from study procedures. Each box of probiotics/placebo is expected to last 30 days. Participants will be provided with enough supplies for the duration of the study period.

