All adverse events during the study period will be recorded, and these records will be maintained for 15 years. The clinical trial sponsor will inform the Natural and Nonprescription Health Product Directorate of Health Canada of any serious expected or unexpected adverse events related to the study product immediately if possible and no later than 7 days after becoming aware of the information. Reported symptoms of psychosis (hallucinations, delusions, or disordered thinking) will trigger a referral of participants to the study psychiatrist for assessment and to determine whether they meet the criteria for withdrawal. If a participant reports a significant worsening in symptoms of anxiety or depression, they will be permitted to remain enrolled in the study but will be advised to contact their primary mental healthcare provider for assessment and management. If the mental healthcare provider suggests that psychiatric rescue medication is needed, this clinician will recommend the treatment to the participant. Changes to treatment regimens must be reported to the study team for documentation.

Serious adverse events will also be reported to the research ethics boards that have reviewed the study protocol.

Participants who complete all parts of the study but fail to adhere to regular supplemental intake (defined as missing 7 or more consecutive days), will be included in the study for as long as they wish. Their reasons for not taking the supplements will be documented, and strategies to help overcome this (i.e., forgetfulness) will be made. If the reasons for stopping supplements are allergic reactions or side effects, they will be withdrawn from the intervention, and an adverse report will be made consistent with the safety protocol. If participants still wish to continue with the study, they may do so as part of the control arm.

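### The continuation stage is meant to assess each intervention, but every randomised woman takes fish oil, so fish oil's own effect has no randomised comparator at any sample size

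*Protocol article*

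**What the plan says.** All references are to the protocol article.

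- **Aim.** Microbiome profiling says that a successful feasibility trial will continue enrolling with the goal of "assessing the efficacy of the interventions and specifically the impact of each on the gut microbiome and mental health outcomes". The Objectives name three interventions: a high-fibre diet, probiotics and fish oil.
- **Exposure.** The intervention: "Participants in all intervention groups will receive a 200-ml bottle of Genestra brand Super EFA Forte Liquid Omega-3 Fatty Acid". In the randomised arm with the least treatment, "participants in the Gutless arm will receive fish oil and a placebo" (Trial design and setting).
- **Placebo.** The placebo capsule is "identical in capsule shape and packaging to the probiotics" (Investigational products). No placebo oil is described.
- **Randomisation.** Women who accept both products and the placebo "will be fully randomized to one of the intervention arms" (Trial design and setting), "using permuted blocks of three and six" (Exclusion criteria). Women who will not or cannot take placebo or probiotic are placed, without randomisation, in a group that suits them.
- **Control.** "Participants unable or unwilling to take any of our investigational products will be assigned to the active control arm" (Trial design and setting). A second route in exists for women taken off the intervention because of allergy or side effects: "If participants still wish to continue with the study, they may do so as part of the control arm" (Criteria for study withdrawal).
- **Use of control.** All four arms are to be compared on the microbiome (Microbial response to diet and supplementation). The ANCOVA compares the groups on EPDS and GAD-7 (Statistical analysis). The Discussion expects control to help show the size and direction of changes.

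**The concern.** An aim to assess each intervention implies an estimate for fish oil as well as for probiotic and diet. The allocation supplies a randomised estimate for the last two only. For fish oil, a reader would have to turn to Gutless versus control. That contrast mixes the oil with willingness and ability to take supplements, with capsule taking, and with expectation, since control women receive no study product and know it. At stake is whether the continuation stage could publish a fish-oil finding on perinatal mood or microbiome that its design cannot support.

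**Working it through.** The plan gives no power or precision figure to reproduce. The question is what the allocation can identify.

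**Step 1: code the arms** as (fish oil, probiotic, diet), from Trial design and setting and The intervention.

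| Arm | Fish oil | Probiotic | Diet | Allocation |
|---|---|---|---|---|
| Gutopia | 1 | 1 | 1 | randomised, or by preference |
| Gutboost | 1 | 1 | 0 | randomised, or by preference |
| Gutless | 1 | 0 | 0 | randomised, or by preference |
| Control | 0 | 0 | 0 | never randomised |

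**Step 2: what the randomised arms identify.** The model has four parameters: intercept, fish oil, probiotic, diet.

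- Three randomised arms: rank 3 of 4. The fish-oil column equals the intercept column, so its effect cannot be separated.
- Gutboost minus Gutless = (1,1,0) − (1,0,0) = (0,1,0): probiotic added to fish oil.
- Gutopia minus Gutboost = (1,1,1) − (1,1,0) = (0,0,1): diet counselling added to both supplements.
- With control included: rank 4 of 4. Fish oil becomes estimable, but only as Gutless minus control = (1,0,0).

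The result does not depend on the number of women per arm.

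**Step 3: is control randomised?** Trial design and setting says it is not. Block sizes agree: 3 and 6 are multiples of three arms and not of four. The Abstract instead says that the 100 women are randomised into four arms, control included. The two statements conflict; the detailed Methods and the blocks support three randomised arms.

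**Step 4: can the planned analysis repair the control contrast?**

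- The ANCOVA covariates are pharmacotherapy, exercise status and psychotherapy. Neither route of allocation nor baseline score is listed.
- Mental health outcome and Microbial response to diet and supplementation also plan comparisons of change from baseline. These remove a constant baseline gap but not a difference in trajectory.
- Within-group change in Gutless is uncontrolled and runs together with gestation and postpartum time.
- Non-study natural health products are allowed (Concomitant therapies) and fatty-acid blood markers are not measured (Microbiome profiling), so fish-oil intake in control is known from self-report only.

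**Step 5: illustration of why enrolment does not help.** Assume no fish-oil effect and a selection gap of b SD in the quantity being compared. The values of b and the 100 per arm are assumptions; 25 is the planned control size and one third of the 75 in the intervention arms. With t = b / √(2/n), the two-sided 5% test rejects with probability Φ(t − 1.96) + Φ(−t − 1.96).

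| b (SD) | t, n = 25 | Rejects | t, n = 100 | Rejects |
|---|---|---|---|---|
| 0.2 | 0.71 | 11% | 1.41 | 29% |
| 0.3 | 1.06 | 19% | 2.12 | 56% |
| 0.5 | 1.77 | 42% | 3.54 | 94% |

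The bias stays fixed while the standard error shrinks, so false-positive risk rises with n.

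**The case against.** **The phrase may mean arms rather than components.** The article uses the word intervention for both. It states no hypothesis about fish oil alone, and the contrasts it names are Gutboost versus Gutless and Gutopia versus the other intervention arms. This stands in part: a reader might infer that the plan commits to reading Gutless versus control as a fish-oil effect, and no sentence says so. But the Objectives count fish oil as an intervention, and on the arm reading the Gutless package still has no randomised comparator without fish oil. Comparisons with control remain planned.

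**Preference allocation is open and deliberate, and the efficacy stage is conditional and only outlined.** True. That justifies having the control arm, not drawing efficacy conclusions from it. Because enrolment is to be continued and no new allocation is described, the limitation carries over.

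**Selection need not bias every analysis in full.** Correct. A constant baseline gap cancels in a change score, and screening for absence of current depression and anxiety limits baseline gaps. It would be too strong to say that any prior difference passes whole into the estimate; what remains is difference in trajectory.

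**Two further stronger readings fail.** A reader might take all 75 women in the intervention arms as randomised, but some may be assigned by preference and the number randomised is not given. A reader might also describe controls as women who refused everything; the text says unable or unwilling, and adds those withdrawn for side effects.

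**Conclusion.** The point holds. No randomised woman goes without fish oil, so randomisation under the described allocation cannot estimate its effect, whatever the sample size. The only between-group evidence is a non-randomised, unblinded contrast with a self-selected group, and neither the listed ANCOVA covariates nor change scores remove a difference in trajectory.

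The identifiability result rests on the arm definitions alone. The false-positive rates rest on assumed gaps and show direction rather than a forecast. A reader might infer that the trial as a whole is undermined; the documents do not support that. The primary outcome is process evaluation and is unaffected, and the probiotic and diet add-on effects do have randomised contrasts, provided they are restricted to randomised women.

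**What to change.** 1. **Microbiome profiling:** limit the efficacy aim to two effects, estimated in randomised women only: probiotic added to fish oil (Gutboost versus Gutless) and diet counselling added to both supplements (Gutopia versus Gutboost). State that the effect of fish oil alone is not estimated by this design.
2. **Microbial response to diet and supplementation, Statistical analysis, and Discussion:** label every comparison with control as descriptive and non-randomised, and exclude it from efficacy conclusions.
3. **Abstract:** reconcile the statement that all 100 women are randomised to four arms with Trial design and setting and the block sizes.

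The cost is a few sentences. The sponsor gives up a fish-oil efficacy claim, and the randomised-only contrasts use somewhat fewer women, by a number that the article does not let one calculate.
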